#### Human-centred design framework

App design took a human-centered approach, guided by the IDEAS (Integrate, Design, Assess, and Share) Framework [36]. IDEAS is a design framework and toolkit for the human-centred development of digital behavior change interventions that can be used to engage participants throughout the intervention development and is composed of 10 phases of design (empathise, specify, ground, ideate, prototype, gather, build, pilot, evaluate, and share), grouped into 4 stages: Integrate, Design, Assess, and Share (IDEAS). To develop features and content, parents and researchers worked together via video conferencing interviews to develop and evaluate a series of prototype features and content that may help parents adopt child-centred responsive feeding practises and discourage the use of authoritarian-style parent feeding practises, such as persuasive/coercive feeding. Primary features include (1) a Tracker that allows parents to keep track of the times they’ve offered specific foods to their child and to track their child’s response, (2) topics that provide information on why toddler fussy eating behaviour is normal, child-centred feeding strategies to adopt, and how much food toddlers need, (3) rescues, which are quick references to material that support the Topics contents (e.g. lists of non-food rewards, tips for managing food-related tantrums, ideas for addressing food waste concerns), and (4) recipes (a variety of healthful, simple recipes with a variety of vegetable ingredients were sourced from the My Baby Now app [57] and adapted to be age-appropriate for toddlers).

#### Intervention delivery

Participants in the intervention group will be sent an email with instructions for how to access the intervention app to their personal smartphone. The email will contain a link to the webpage where the web app is hosted, their username, and a temporary password. Participants will be required to set a new password the first time they access the app. Parents will be instructed to either (1) place a bookmark to the web app on their phone’s home screen or (2) install the web app to their phone, which will deliver a ‘native-like’ experience to participants.

Across the 6 weeks of the intervention, participants will receive SMS messages that contain feeding tips and links to the app, prompts to reengage with the app, and summaries of their activities on the app (e.g. summary of food offers tracked that week). In line with the evidence that personalised, tailored information supports behaviour change interventions, the SMS messages will be tailored to each participant based on child’s age, current feeding practises, feeding goals, and their own preferences (e.g. time of day, day of week, frequency).

### Control

Participants randomised to the control group will be wait-listed for the app and continue to receive any usual care. After a 6-week period, parents in the control group will complete follow-up measures and then be granted access to the app to the app.

### Participant compensation

Participants will be compensated for their time with a shopping gift voucher ($20AUD for each questionnaire completed—baseline and post-intervention—and $20AUD for participating in a post-intervention interview).

### Outcome measures

All measures will be collected at baseline and 6 weeks later at completion of the study. Outcomes will be assessed using online questionnaires, and app usage statistics will be collected throughout the study period.

#### Primary outcomes

The primary outcomes of this study relate to feasibility and acceptability of the intervention and the app platform: participant retention rate, intervention engagement, app usability, perceived ease in using the app, perceived usefulness of the app, and user satisfaction. Feasibility and acceptability outcomes will be assessed with data from the intervention group only. The measures for primary outcomes are provided in \* MERGEFORMAT Table 1.

**Table 1 Tab1:** Feasibility and acceptability criteria and measures for the Fussy Eating Rescue pilot trial

Measures	Feasibility and acceptability criterion
Participant retention rate	At least 80% of enrolled participants complete the 6-weeks post-intervention questionnaire
Intervention engagement	At least 80% of intervention participants begin engaging with the app There are currently not standards of practice for what constitutes acceptable app engagement in digital health interventions for parents (58) App usage metrics will be explored and reported (e.g. session interval, session length, time in app, screen flow, retention, SMS received/read)
Usability of the app platform	Average System Usability Scale (SUS) [58] scores meet or exceed benchmark of 81 (the average score of the final usability tests before the pilot)
Perceived ease in using the app platform	Average mHealth App Usability Questionnaire (MAUQ) [59] scores are 80% of highest score possible
Perceived usefulness of the app platform	Average MAUQ ease of use, usefulness, and satisfaction subindex scores are 80% of highest score possible
Satisfaction with the app platform	Post-intervention interviews will explore further parents’ experiences using the app, including usability and acceptability, positive and negative aspects of the app, impact of the app on their life, and facilitators/barriers to using the app

#### Secondary outcomes

Secondary outcomes include parent feeding practises and children’s eating behaviours. Secondary outcomes will be measured using validated tools included in both the pre- and post-intervention questionnaires. Parent feeding practises will be captured using relevant subscales from the Child Feeding Practises Questionnaire (CFPQ, i.e. modelling) [60] and the FPSQ (family meal setting, persuasive feeding, reward for eating, and structured meal timing) [61]. The practise of repeated exposure will be measured with one question validated for this purpose [62]. Children’s food fussiness will be measured with the Food Fussiness subscale of the Child Eating Behaviour Questionnaire (CEBQ) [63]. Children’s specific food avoidance behaviours (e.g. eating slowly, hiding food, gagging) will be inventoried with the Meal Behaviour Questionnaire (MBQ) [64].

#### Demographics

On the baseline questionnaire, parents will report their age, highest level of education, relationship to their child (e.g. biological father, step-mother, other), family income (reported as: less than $40,000, $40,000–$49,000, $50,000–$59,000, $60,000–$69,000, $70,000–$79,000, $80,000–$89,000, $90,000–$99,000, $100,000–$149,000, and more than $150,000), household size, post code, employment status, country of birth, and the main languages spoken at home. Parents will also report their child’s age and gender, height, and weight.

### Analysis

Analysis of primary outcomes, related to feasibility and acceptability, will only be available from the intervention group and therefore cannot be blinded. Analysis of secondary outcomes, which will be collected from intervention and control participants, will be blinded. Data will be analysed with R [65] using RStudio software [66]. Frequencies and proportions will be calculated for categorical data; means and standard deviations will be calculated for continuous data; medians and IQRs will be calculated for ordinal data. Descriptive statistics derived from usage data will be used to characterise the engagement and acceptability of the intervention app. Specifically, building upon previous research conducted by the research team, an engagement index will be calculated from five subindices: click depth, loyalty, interaction, recency, and feedback [67, 68]. Although this pilot RCT will not be powered to detect intervention effects, the within-group mean differences and 95% CIs will be reported for changes in secondary intervention outcomes between baseline and 6 weeks. The standardised mean differences between intervention and control groups will be interpreted as 0.2 = small effect, 0.5 = moderate effect, 0.8 = large effect, and 1.2 = very large effect [69].

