Fussy eating most commonly begins in early toddlerhood (12 to 24 months) and peaks in intensity in later toddlerhood (24 to 36 months) [21, 22]. The evidence suggests that most toddlers described as ‘fussy eaters’ by their parents are likely exhibiting developmentally typical eating behaviours that are likely to resolve as children age [20]. However, nonresponsive feeding practises may increase the intensity of and duration of fussy eating behaviours [9–12]. Therefore, targeted interventions that addresses parents’ concerns for their toddlers’ fussy eating behaviours are warranted.

Parents of young children have expressed a preference to engage digitally with health promotion content [23, 24]. An important advantage of digital health interventions is that they allow participants to access content at any time and any place of their choosing, which may mitigate barriers related to transportation, childcare, and scheduling conflicts [25–27]. Using digital platforms also provides opportunities to tailor content so that it is perceived to be personally relevant to the user [28]. Further, digital health interventions may also have advantages related to cost [29, 30] and scalability [25].

Previous digital parent feeding interventions have shown promise in improving parents feeding practices [31, 32]; however, no digital intervention has been developed to improve the feeding practises specifically among parents of toddlers concerned for fussy eating. Given the high proportion of parents concerned about fussy eating [8, 18–20], evidence that underlying fussy eating may undermine child nutrition interventions [33], and the general need for effective, scalable parent-centred feeding interventions [34], the development of successful interventions among this population is warranted.

The primary aim of this study is to assess the acceptability and feasibility of Fussy Eating Rescue, a fully-automated web app that aims to improve the feeding practises of parents concerned for toddler fussy eating behaviours. Primary feasibility measures include assessing participant retention rate, intervention engagement, app usability, perceived ease in using the app, perceived usefulness of the app, and user satisfaction. A secondary aim is to explore any indications of intervention effect.

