## Methods

### Design

This protocol describes a 6-week, two-arm, parallel, randomised control pilot trial to evaluate a purely web app based intervention to improve the feeding practises of parents of toddlers (12–36 months) who are concerned for their toddler’s fussy eating behaviours. Parents assigned to the intervention group will have access to the web app containing information, strategies, recipes, and activities to track feeding attempts. Parents in the intervention group will also be able to opt into receiving to 42 SMS messages across the 6 weeks with tips and prompts to revisit the app. Pre and post-measures collected from a control group of parents (placed on a six week waitlist) will be used to evaluate indications of intervention effect. The description of the protocol and intervention are in line with the CONSORT guidelines for randomised pilot and feasibility trials [35]. A CONSORT diagram is provided in \* MERGEFORMAT Fig. 1 and the CONSORT checklist. The trial is prospectively registered at the Australian New Zealand Clinical Trials Registry (ACTRN12621000925842) and ethics approval was obtained from Deakin University Human Research Ethics Committees (2021–139).

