### Study sample and recruitment

Parents who self-identify as concerned for the fussy eating behaviours of their toddler (12–36 months old) will be recruited via paid Facebook advertisements. The Facebook advertisement audience settings will be used to target adults (18–45 years) living in Australia who have general interests related to parenting toddlers. To address a common issue of study recruitment involving the overrepresentation of participants with relatively high socioeconomic position, a geographic location parameter will also be used to preferentially show advertisements to Facebook users who live in postcodes in the lower 2 deciles of the Socio-Economic Indexes for Areas (SEIFA), a product developed by the Australian Bureau of Statistics that ranks Australian areas based on measures of relative socio-economic advantage and disadvantage [37]. Participants will be eligible for inclusion if they currently live in Australia, are able to read and write in English, have a mobile phone that can access the internet and care for a child who is 12–36 months old and lives with them at least half of the time. The intervention has been developed to address the concerns of parents whose children display developmentally typical eating behaviours and have no co-existing conditions that present additional nutritional risk. Given this, participants will be excluded if they indicate that their child has been diagnosed with autism spectrum disorder, learning difficulties, avoidant/restrictive intake disorder, or a medical condition that requires them to follow special dietary requirements (e.g. type 1 diabetes, cystic fibrosis, celiac disease, or metabolic conditions).

Individuals who click on the Facebook ads will be taken to a REDCap screening survey hosted at Deakin University [38]. Eligible participants will be provided with a written introduction to the study and a plain language statement outlining the study protocols before providing informed consent.

Informed by evidence from the literature on sample size requirements for pilot RCTs, it is estimated that a sample of 40 participants will generate sufficient data to determine the feasibility of the intervention [39, 40]. To allow for a potential 20% attrition rate, a total of 50 participants will be recruited.

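### The 95% intervals are placed on within-group change, while the randomised between-group comparison gets an effect-size label and no stated interval

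*Protocol article*

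**What the plan says.** The last paragraph of the protocol article's Background states: "A secondary aim is to explore any indications of intervention effect". The Design section gives the control group's pre and post measures the matching role: they "will be used to evaluate indications of intervention effect".

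The Analysis section then makes two choices for the secondary outcomes. First, "the within-group mean differences and 95% CIs will be reported for changes in secondary intervention outcomes between baseline and 6 weeks". Second, "The standardised mean differences between intervention and control groups will be interpreted as 0.2 = small effect, 0.5 = moderate effect", with 0.8 and 1.2 as the thresholds for large and very large. No confidence interval or other measure of uncertainty is stated for the between-group SMD. The same section acknowledges that "this pilot RCT will not be powered to detect intervention effects".

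**The concern.** A within-group change mixes any effect of the app with everything else that moves scores over six weeks. The article itself gives two reasons to expect movement in both arms. Parents enter because they are currently concerned (Study sample and recruitment), which makes regression to the mean plausible. The Background also describes the behaviours as mostly typical for age and tending to resolve, though it gives no time scale. An interval around such a change does not estimate an intervention effect. Finding that one arm's interval excludes zero and the other's does not is no evidence of a difference between arms.

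The SMD between arms does address the stated aim, but it is to be read through a size word with no indication of its precision. In a sample this small, a reader could take a label of small or moderate as an indication of effect when chance alone produces it often.

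**Working it through.** **The plan's own figure.** The article says "it is estimated that a sample of 40 participants will generate sufficient data to determine the feasibility of the intervention" and "To allow for a potential 20% attrition rate, a total of 50 participants will be recruited". Check: 40 / (1 - 0.20) = 50, which reproduces. No power, significance level or effect size is given for the secondary outcomes, so there is nothing else to reproduce.

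**Inputs.**
- Arm size: 25 randomised per arm (Study sample and recruitment). I assume 20 completers per arm, from 40 evaluable with equal attrition, and also show 25.
- Scales: 8 (Secondary outcomes): one CFPQ subscale, four FPSQ subscales, one repeated-exposure item, CEBQ Food Fussiness and the MBQ.
- SMD: taken as a difference in means divided by the SD of the same score. The article does not define it.

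**Precision of the SMD.** SE = sqrt(2/n + d²/(4n)).
- n = 20, d = 0.5: sqrt(0.100 + 0.25/80) = 0.321; 0.5 ± 1.96 × 0.321 gives -0.13 to 1.13.
- n = 20, d = 0.2: -0.42 to 0.82.
- n = 25, d = 0.5: -0.06 to 1.06.

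**How often a label appears with no true effect.** At d = 0, SE = sqrt(2/n), which is 0.316 at n = 20 and 0.283 at n = 25. The two-sided tail comes from the central t distribution with 2n - 2 degrees of freedom.

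| Absolute SMD at least | 20 per arm | 25 per arm |
|---|---|---|
| 0.2 | 0.53 | 0.48 |
| 0.5 | 0.12 | 0.08 |
| 0.8 | 0.016 | 0.007 |

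**Across the 8 scales.** The chance of an SMD of 0.5 or more in the favourable direction on one scale is 0.122/2 = 0.061 at 20 per arm. Treating the scales as independent, the chance of at least one is 1 - (1 - 0.061)^8 = 0.40. At 25 per arm it is 0.29.

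**Sensitivity to how the SMD is defined.** Suppose change scores are standardised by the baseline SD, with an assumed pre-post correlation r of 0.7. The variance is multiplied by 2(1 - r) = 0.60, so SE is about 0.316 × sqrt(0.60) = 0.245. An observed 0.5 then has an interval of about 0.5 ± 0.48, or 0.02 to 0.98. That is narrower, but still runs from below small to above large.

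**Within-group intervals.** Suppose both arms improve equally and the app does nothing. Let m be the common change in units of the SD of change (assumed range 0.2 to 0.6; the article gives no figure). With 20 per arm, the chance p that one arm's 95% CI excludes zero comes from the noncentral t with 19 degrees of freedom and noncentrality m × sqrt(20). The chance that exactly one arm's CI excludes zero is 2p(1 - p).

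| m | p | Exactly one arm | Intervention arm only |
|---|---|---|---|
| 0.2 | 0.136 | 0.235 | 0.117 |
| 0.4 | 0.397 | 0.479 | 0.239 |
| 0.6 | 0.721 | 0.402 | 0.201 |

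So a pattern of change in one arm only would be common without any effect.

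**The case against.** **The SMD is already the randomised comparison.** A reader might infer that the indications of effect will rest on a non-randomised comparison. The documents do not support that. The SMD contrasts the randomised arms, and nothing says an effect will be inferred from one arm's interval excluding zero. The within-group calculation shows how such a reading would mislead, not that it is planned. What remains is that the randomised contrast has no stated interval.

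**The labels do not drive the next trial.** A reader might also infer that they will set the larger trial's sample size. No section says so. The Abstract ties the larger trial to feasibility and acceptability, and no secondary outcome appears among the Table 1 criteria.

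**The article is silent on detail.** It does not say how the SMD is computed, so it cannot be said to ignore the baseline values or to rule out an interval on the SMD. A fuller protocol or analysis plan may settle both. This stands for baseline adjustment, which belongs in the remedy and is not itself a fault. It does not dispose of the main point: the article states which quantity gets the interval and how the between-group result is to be read.

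**The trial is openly unpowered and exploratory.** This is true, and it limits the severity. It is also the reason an interval is needed, since a size word alone hides the acknowledged imprecision. Reporting an interval requires no hypothesis test.

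**The multiple-scale figure is an upper-end case.** This stands. Four of the eight scales come from one questionnaire, so independence is unlikely. The single item and the MBQ inventory may be summarised as ordinal data and yield no SMD; with six scales the figure is 1 - 0.939^6 = 0.31. Counting either direction over eight scales gives 0.65, but that should not be read as the chance of a spurious benefit.

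**Conclusion.** The point holds as a moderate, should-fix matter. The stated 95% intervals are on a quantity that does not use the control arm, while the contrast that answers the secondary aim is given a label without one.

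At the assumed 20 completers per arm, the cut-offs of 0.2 and 0.5 both lie inside the 95% noise band of about ±0.62 to 0.64 around zero. At 25 per arm the band is about ±0.55 to 0.57, and the 0.5 cut-off is still inside it. These figures rest on equal attrition and on the SMD definition used above. The figure of about 40% for at least one favourable moderate label further assumes eight independent scales.

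The primary feasibility and acceptability criteria are unaffected.

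**What to change.** Revise the two sentences in the Analysis section along these lines: for each secondary outcome, the between-group difference at 6 weeks, adjusted for its baseline value, will be reported with a 95% CI, and as an SMD (standardiser stated) with its 95% CI; within-group changes will be descriptive only; any size label will be shown beside the interval.

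The cost is wording only, because the outcomes are already collected at baseline and 6 weeks in both arms. Adjustment should also improve precision. For an assumed pre-post correlation r of 0.5, 0.7 or 0.8, the relative variance is 1 - r² = 0.75, 0.51 or 0.36 with adjustment, against 2(1 - r) = 1.00, 0.60 or 0.40 for change scores and 1.00 for follow-up scores alone. The reported effects will look less certain, which reflects what a sample of this size can show.

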## Discussion

The current study is designed to evaluate the acceptability and feasibility of an mHealth intervention to improve the feeding practises of parents concerned for toddler fussy eating behaviours. This study will also assess a range of secondary outcomes including parent feeding practises, parent outcome expectations, parent capabilities, and children’s eating behaviours.

Responsive feeding practises have been shown to have beneficial impacts on children’s health and diet, especially for children with fussy eating behaviours [70]. However, parents concerned for fussy eating often respond with nonresponsive feeding practises that increase the severity and duration of fussy eating behaviours and have myriad negative impacts on children’s and parents physical and mental health [11, 18].

Previous studies have shown that are increasingly relying on digital platforms as sources for health information and support [71, 72]. However, no previous digital health interventions to improve the feeding practises of parents concerned for toddler fussy eating have been evaluated. A key factor in the success of digital health interventions is participant engagement [73] hence, it is critical to incorporate user-centred design methods and to evaluate feasibility and acceptability before proceeding to larger trials. We speculate that Fussy Eating Rescue intervention—developed via iterative design cycles that incorporated parent feedback—will be acceptable, feasible, and will promote responsive feeding practises among parents concerned for fussy eating. 

## Data Availability

The datasets generated and/or analysed during the current study are not publicly available but are available from the corresponding author on reasonable request.
